#### Secondary trial outcomes

The following are the secondary trial outcomes:
The proportion of all antenatal clinic appointments (at ‘first appointment’, 27–28 weeks gestation, and 35–36 weeks gestation) for which clients report receiving all elements of the gestational weight gain care pathway (‘complete gestational weight gain care’):
An assessment of gestational weight gain using objective measures of weight against recommended weight gain targetsAdvice on gestational weight gain, dietary intake, and physical activityOffer of a referral to the NSW GHiP Service and, for women who are gaining weight above or below their recommended weight gain target, and where available, offer of a referral to a dietetics service (including culturally appropriate dietetics services for Aboriginal women)The proportion of women attending antenatal clinic appointments (at ‘first appointment’, 27–28 weeks gestation, and 35–36 weeks gestation) that report accepting a referral to the NSW GHiP Service and, for women who are gaining weight above or below their recommended weight gain target, and where available, accepting a referral to a dietetics service (including culturally appropriate services for Aboriginal women)The proportion of women that report weight gain within the recommended ranges at 28 weeks and 36 weeks gestation based on the IOM recommendations according to the four categories of pre-pregnancy BMI (underweight, healthy weight, overweight, and obese)Estimated average rate of weekly weight gain at 28 weeks and 36 weeks gestation, according to the four categories of pre-pregnancy BMI (underweight, healthy weight, overweight, and obese)Mean maternal diet quality score at 28 weeks and 36 weeks gestation calculated by an 11-item food frequency questionnaire based on the Australian Guide to Healthy Eating [52]Mean total maternal physical activity levels (minutes/week) at 28 weeks and 36 weeks gestation assessed using the 7-item International Physical Activity Questionnaire (IPAQ) short form, which has been found to be both reliable and valid in assessing physical activity in adults [64]

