### Statistical analysis

Pre- and post-intervention primary outcome data will be analysed using mixed effects logistic regression models to detect a change in the reported receipt of each of the three elements of the best practice care pathway for addressing gestational weight gain (assessment, advice, and referral) for all three sectors combined. Separate models will be fitted for each outcome. The main predictor of interest will be a before/after intervention indicator variable as well as a fixed effect for time, and a random intercept for an antenatal time point (first appointment, ‘27–28 weeks gestation’, or ‘35–36 weeks gestation’). The implementation intervention will be declared effective if the coefficient for the intervention period variable is below the threshold of *α* = 0.0167 for any of the three primary outcomes. A time-series analysis will be performed over the post-intervention periods to determine if slope changes occur, as an indicator of sustainability. Pre- and post-intervention secondary outcome data will be analysed using mixed effects logistic regression models to detect a change in each outcome for all three sectors combined. Descriptive statistics will be used to report on the process measures. The cost analysis and practice change cost-effectiveness results will be incorporated into an economic model to project the expected costs and outcomes that would be associated with broader scale-up of the implementation intervention to antenatal services across the state. SAS (V9.3 or later) will be used for all statistical analyses.

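### Logistic regression is assigned to every secondary outcome, but three of the six are numeric and need a model for a mean

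*Protocol article*

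**What the plan says.** The Statistical analysis section gives one sentence on the model for the secondary outcomes: "Pre- and post-intervention secondary outcome data will be analysed using mixed effects logistic regression models to detect a change in each outcome", for the three sectors combined. It makes no exception and names no second model.

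The Secondary trial outcomes section defines six outcomes. Three are proportions:

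- complete care, the share of appointments "for which clients report receiving all elements of the gestational weight gain care pathway";
- referral uptake, the share of women "that report accepting a referral to the NSW GHiP Service" and, where applicable, a dietetics referral;
- "The proportion of women that report weight gain within the recommended ranges at 28 weeks and 36 weeks gestation".

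Three are on a numeric scale:

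- "Estimated average rate of weekly weight gain at 28 weeks and 36 weeks gestation", to be given by four categories of pre-pregnancy BMI;
- "Mean maternal diet quality score at 28 weeks and 36 weeks gestation", from an 11-item food frequency questionnaire;
- "Mean total maternal physical activity levels (minutes/week) at 28 weeks and 36 weeks gestation", from the short-form International Physical Activity Questionnaire.

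**The concern.** The outcome definitions and the analysis sentence do not fit together. Logistic regression models the probability of falling in a category. The last three outcomes are defined as an average rate, a mean score and mean minutes, so the effect of interest is a difference in means, which a logistic model does not produce.

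An analyst holding this text has two options. One is to follow it literally, which requires turning the three measures into categories that the article does not define, and so answers a different question. The other is to fit a model for the mean, which is a departure from the published plan; the section on trial discontinuation or modification commits the investigators to reporting deviations.

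The abstract names diet quality and physical activity among the secondary outcomes, and these numeric measures are the only diet and activity outcomes listed. The section on within-trial economic analyses also takes the secondary outcomes into the cost-consequence analysis, where effects in natural units are the useful form.

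**Working it through.** The plan states no figure on this point that could be reproduced. The check sets each outcome's definition beside the model assigned to it.

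| Secondary outcome | Defined as | Response per interview | Assigned model | Match |
|---|---|---|---|---|
| Complete care | Proportion | Yes/no | Logistic | Yes |
| Referral accepted | Proportion | Yes/no | Logistic | Yes |
| Weight gain within range | Proportion | Yes/no | Logistic | Yes |
| Weekly rate of weight gain | Average rate | Numeric | Logistic | No |
| Diet quality | Mean score | Numeric | Logistic | No |
| Physical activity | Mean minutes/week | Numeric | Logistic | No |

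Count: 6 outcomes, 3 matched, 3 not matched.

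1. *Can the named model be fitted to the numeric outcomes as they stand?* No. The binary logistic model is logit P(Y = 1) = linear predictor, with Y equal to 0 or 1. As a confirmation, a binary logit was tried on 500 simulated minutes-per-week values (assumed normal, means 150 and 170, SD 80). The software refused it because the response must lie in the unit interval.

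2. *Does the article supply a categorisation that would make it work?* No. No cut point is given for rate of gain, diet score or activity minutes. The four pre-pregnancy BMI categories group the women; they do not categorise the rate of gain.

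3. *Does another sentence assign a different model?* No. The only other methods in the Statistical analysis section are the logistic models for the primary outcomes, a time-series analysis of slope changes after the intervention, descriptive statistics for process measures, and an economic model.

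4. *What would dichotomising cost, if someone did it?* For a normal outcome cut at its median, the large-sample efficiency relative to comparing means is 2/π = 0.637, a loss of 1 − 0.637 = 0.363. This is illustrative only: the plan states no dichotomisation and gives no distribution for any of the three outcomes. Nor should the 36% be applied to all 5600 data points. These outcomes are defined at two of the three antenatal time points. At the planned 15 interviews per time point per week, that is 30 of 45, or about 5600 × 30/45 ≈ 3733.

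**The case against.** The best defence is that this is drafting shorthand. The sentence closely follows the one for the primary outcomes, the article is condensed, and a statistical analysis plan may name linear models. The trial's aim is care provision. The primary analysis, the alpha of 0.0167, the effectiveness rule, the sample size and data collection do not depend on the sentence. It can be corrected before analysis, and the article provides for updating the registration record. All of that stands, and it limits the consequence. It does not remove the error: the article is not silent here but names a model and applies it to each secondary outcome.

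A second defence is that logistic models are not confined to binary data, since a cumulative logit mixed model could take an ordered diet score without a cut. That is true, but the article specifies no such model, and it would give a cumulative odds ratio, not a difference in the mean score that defines the outcome.

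Two stronger readings are tempting and not supported:

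- A reader might infer that the investigators intend to dichotomise and will lose about a third of the information. The article mentions no cut points, and it fixes the outcomes as means and a rate. The evidence is of a misnamed model, not a plan to dichotomise.
- A reader might infer that the trial loses its main evidence on weight. It does not: the proportion gaining within the recommended ranges is binary and correctly matched to logistic regression. Only for diet and activity is there no other listed outcome.

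**Conclusion.** The point holds as a mismatch between two sections of the article. For 3 of the 6 secondary outcomes the stated model cannot estimate the quantity the outcome defines. The primary outcomes and the three secondary proportions are unaffected, so the trial's main conclusion is not at risk.

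The conclusion rests only on the outcome definitions and the analysis sentence, not on any assumed variance, distribution or sample size. The count of three in six is the firm measure of size; no percentage loss of information can be attached to this trial from the documents. The text should be corrected before analysis, so that the choice of model for these outcomes is not left until the data are in view.

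**What to change.** Replace the single sentence on secondary outcomes in the Statistical analysis section with text to this effect:

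- Complete care, referral acceptance and weight gain within the recommended range: mixed effects logistic regression, as now.
- Weekly rate of weight gain, diet quality score and physical activity minutes: mixed effects linear models with the intervention indicator, a fixed effect for time and a term for the 28- versus 36-week time point, reporting adjusted mean differences with confidence intervals. The time-point structure should be written out for these models, because they have two time points where the primary outcomes have three.
- Rate of weight gain: results given by the four pre-pregnancy BMI categories, as the outcome is defined.
- Physical activity minutes: a pre-specified alternative model for the mean, suited to skewed data, with the criterion for using it stated in advance. Marked skewness is an assumption, as the article gives no distribution.

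The cost is analysis wording and an update to the registration record. Data collection, sample size and trial conduct do not change.

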### Research trial governance

A research co-production approach has been employed in the development and design of the study [70]. The conduct of the study will similarly be overseen by an advisory group consisting of researchers, policymakers, practitioners, and clinical experts with expertise related to gestational weight gain, nutrition, physical activity, health promotion, implementation science, health economics, study design and statistics, Aboriginal health, obstetrics, and midwifery. A project team consisting of research staff and practitioners will develop and operationalise implementation strategies and data collection components of the trial according to the study protocol. Implementation leadership groups established within each of the three participating sectors will provide advice on the aspects of the gestational weight gain care pathway and implementation strategies that require sector-specific tailoring and oversee the delivery of the implementation intervention in their sectors.

Aboriginal people will be included at all stages of project governance, including the abovementioned advisory group, project team, and sector-specific implementation leadership groups. A series of Aboriginal cultural governance task groups, co-led by Aboriginal and non-Aboriginal staff, will provide guidance on cultural considerations for Aboriginal and Torres Strait Islander people relating to the gestational weight gain care pathway, implementation strategies, data collection, and interpretation and dissemination of study findings. A cultural review group containing only Aboriginal members will review all project resources and dissemination products.

### Trial discontinuation or modification

There are no predetermined criteria for trial discontinuation as it is not anticipated that any events would occur that would warrant discontinuing the trial. Any unforeseen adverse events will be reported to the Hunter New England Human Research Ethics Committee (primary approval committee) and advice sought regarding the required action. Any negative effects reported by women regarding the acceptability of weighing and the care they received for gestational weight gain will be monitored and actioned as appropriate. The trial registration record will be updated with any protocol modifications, and any deviations from the original protocol will be reported in study outcome papers.

## Discussion

The research outlined in this protocol will fill an evidence gap regarding the effectiveness of implementation strategies to improve antenatal care addressing gestational weight gain. The findings will directly address Australian policy and practice priorities and needs at a national [8], state [49, 71], and local level [72] and have the potential to be applied at scale in other jurisdictions internationally.

The stepped-wedge design is appropriate for conducting a trial across multiple maternity services where the gestational weight gain care pathway is being introduced as part of routine care at a service level. Study strengths include the theoretical framework and formative surveys used to develop the intervention content, the blinding of data collection staff and survey participants, and the cultural governance model applied to the project. A research co-production approach has been employed in the design of the study and will be employed in its conduct and dissemination, and all study processes and outputs will be reviewed for cultural appropriateness.

## Trial status

Protocol version 1. 4 August 2021. Recruitment of Sector (Site) 1 to commence on 1 September 2021. Recruitment of the last sector (site) to be completed in April 2022.

## Data Availability

Not applicable.

## Abbreviations

AMIHS: Aboriginal Maternal Infant Health Service
BMI: Body mass index
CATI: Computer-assisted telephone interview
CME: Clinical Midwife Educator
HNELHD: Hunter New England Local Health District
NSW: New South Wales
GHiP: Get Healthy in Pregnancy
